## Abstract

**Introduction:**

Congenital diaphragmatic hernia (CDH) is a developmental defect of the diaphragm that impairs normal lung development, causing pulmonary hypertension (PH). PH in CDH newborns is the main determinant for morbidity and mortality. Different therapies are still mainly based on ‘trial and error’. Inhaled nitric oxide (iNO) is often the drug of first choice. However, iNO does not seem to improve mortality. Intravenous sildenafil has reduced mortality in newborns with PH without CDH, but prospective data in CDH patients are lacking.

**Methods and analysis:**

In an open label, multicentre, international randomised controlled trial in Europe, Canada and Australia, 330 newborns with CDH and PH are recruited over a 4-year period (2018–2022). Patients are randomised for intravenous sildenafil or iNO. Sildenafil is given in a loading dose of 0.4 mg/kg in 3 hours; followed by continuous infusion of 1.6 mg/kg/day, iNO is dosed at 20 ppm. Primary outcome is absence of PH on day 14 without pulmonary vasodilator therapy and/or absence of death within the first 28 days of life. Secondary outcome measures include clinical and echocardiographic markers of PH in the first year of life. We hypothesise that sildenafil gives a 25% reduction in the primary outcome from 68% to 48% on day 14, for which a sample size of 330 patients is needed. An intention-to-treat analysis will be performed. A p-value (two-sided) <0.05 is considered significant in all analyses.

**Ethics and dissemination:**

Ethics approval has been granted by the ethics committee in Rotterdam (MEC-2017-324) and the central Committee on Research Involving Human Subjects (NL60229.078.17) in the Netherlands. The principles of the Declaration of Helsinki, the Medical Research Involving Human Subjects Act and the national rules and regulations on personal data protection will be used. Parental informed consent will be obtained.

**Trial registration number:**

NTR6982; Pre-results.

Strengths and limitations of this studyThe Congenital Diaphragmatic hernia Nitric Oxide versus Sildenafil (CoDiNOS) trial is the first randomised controlled multicentre trial to evaluate the effect of intravenous sildenafil and compare with inhaled nitric oxide (iNO) on pulmonary hypertension in newborns with congenital diaphragmatic hernia (CDH).Treatment allocation is not blinded in the trial. This is not feasible because of variability in iNO equipment and gas mixtures use. Instead, the researchers who analyse the echocardiography to evaluate pulmonary hypertension (PH) will be blinded to the treatment.The primary outcome, PH, will be measured using echocardiography instead of just clinical parameters often used in newborns.There is no non-intervention group, as it is common practice in the centres of the CDH EURO Consortium to give iNO; hence, it is considered unethical to withhold treatment for one group.Long-term follow-up of 12 months will give more insight in the course of PH in infants.

## Introduction

Congenital diaphragmatic hernia (CDH) is a severe developmental defect of the diaphragm with an incidence of approximately 1 in 3000 live births and a mortality of 27%.^1^ Because of this defect, the abdominal organs herniate into the chest causing pulmonary hypoplasia and abnormal pulmonary vasculature growth, resulting in pulmonary hypertension (PH).^2^ In adults and children, PH is defined as mean pulmonary artery pressure (mPAP) exceeding 25 mm Hg with a pulmonary capillary wedge pressure of minimal 15 mm Hg.^3^

The normal pulmonary vascular transition of the neonate takes around 2 months to achieve these low values of mPAP. During fetal life, there is high resistance in the pulmonary circulation which results in most of the blood flow to bypass the lungs through the ductus arteriosus and oval foramen. Immediately after birth, the pulmonary vascular resistance drops and the blood flow to the lungs significantly increases.^4^ In contrast, the pulmonary vascular resistance often does not drop adequately in children with CDH due to a decreased vascular bed associated with lung hypoplasia, and an altered development of the pulmonary vasculature with excessive muscularisation of the arterioles, with increased thickness of the arterial media and adventitia. Although the presence of lung hypoplasia can be predicted with prenatal parameters, reliable predictors for PH in CDH patients are lacking.^5^ The incidence of PH in CDH patients is 68%–79% and causes considerable morbidity and mortality.^1 2 6^ Therapy in newborns with PH, such as inhaled nitric oxide (iNO) and sildenafil, has improved outcomes in general. However, trials in infants with CDH are sparse.

iNO diffuses rapidly across the alveolar-capillary membrane into the smooth muscle of pulmonary vessels to activate soluble guanylate cyclase. This enzyme mediates many of the biological effects of iNO, and is responsible for the conversion of guanosine triphosphate (GTP) to cyclic guanosine monophosphate (cGMP). The increase of intracellular cGMP relaxes smooth muscles via several mechanisms. iNO also causes bronchodilation and has anti-inflammatory and anti-proliferative effects.^7^ In term and near term infants with persistent pulmonary hypertension of the newborn (PPHN), iNO decreases the median duration of mechanical ventilation and reduces the need for extracorporeal membrane oxygenation (ECMO). However, in the two available randomised controlled trials (RCT) with a small number of patients with CDH, mortality did not improve and more ECMO treatment was needed despite short-term improvement of oxygenation in some treated patients.^8 9^ In the centres of the CDH EURO Consortium, iNO is standard of care in infants with CDH and PH although the positive pharmacodynamic effects in these infants are less convincing than in infants with PPHN.^6 10^ The pathophysiological mechanism of this difference is not understood. In resource poor settings iNO is often unavailable. In the search to find another treatment option, trials to evaluate the effect of sildenafil in newborns with PPHN have been conducted.^11^

Sildenafil is a selective phosphodiesterase type 5 (PDE5) inhibitor. PDE5 is an enzyme that specifically degrades cGMP. Sildenafil inhibits PDE5, increasing cGMP and nitric oxide-mediated vasodilatation of the smooth muscles in arteries. Only five RCTs have been performed in newborns, all non-CDH patients with PPHN. Four of these studies showed a decrease in oxygenation index (OI) and mortality in a setting where iNO was not available, while one trial showed no additional benefit of sildenafil when added to iNO.^11^ Although sildenafil is increasingly used in CDH patients, only retrospective data are available.^12^ A decrease in pulmonary vascular resistance index and an increase in cardiac output were found in a small group of oral sildenafil-treated infants with CDH refractory to iNO.^13^ Intravenous sildenafil improved OI and reversed the right-to-left shunt ratio over the PDA, but it also increased the need for inotropic support.^14 15^ However, its effect on outcome is unknown.

We hypothesise that intravenous sildenafil is superior to iNO. iNO is the therapy of first choice in most centres despite the lack of evidence, and sildenafil is the most promising drug for the treatment of PH in CDH patients and is increasingly being used.^6 12 16^ However, no studies have been performed comparing iNO with intravenous sildenafil in newborns with CDH and PH or PH alone. Based on the current knowledge, there is equipoise for both treatment modalities.

## Methods and analysis

### Design

The Congenital Diaphragmatic hernia Nitric Oxide versus Sildenafil (CoDiNOS) trial is a prospective, multicentre, international RCT conducted in high volume paediatric surgical centres in Europe, Canada and Australia. The members of the CDH Euro Consortium participating in the trial are listed in the online supplementary appendix.

10.1136/bmjopen-2019-032122.supp1Supplementary data

### Objectives

The primary objective of the study is to determine whether the incidence of PH is lower in CDH patients treated with intravenous sildenafil than in patients treated with iNO, with the primary outcome defined as the absence of PH on echocardiography on day 14 without pulmonary vasodilator therapy and without treatment failure and/or death within the first 28 days after birth. PH is defined as systolic pulmonary arterial pressure >2/3 systolic systemic pressure and/or right ventricular (RV) dilatation/septal displacement and RV dysfunction +/−left ventricular dysfunction.

The secondary outcomes are:

Change in OI after 12 and 24 hours of therapy.Overall mortality.The incidence of treatment failure which is defined as:inability to maintain preductal saturations above 85% (±7 kPa or 52 mm Hg) or postductal saturations above 70% (±5.3 kPa or 40 mm Hg).and/or increase in CO_2_ >70 mm Hg (9.3 kPa) despite optimisation of ventilator management.and/or inadequate oxygen delivery with metabolic acidosis defined as lactate ≥5 mmol/L and pH <7.15 and/or hypotension resistant to fluid therapy and adequate inotropic support resulting in a urine output <0.5 mL/kg/hour.and/or lactate ≥5 mmol/L and pH <7.15.and/or OI consistently ≥40.Time on intervention drug, defined as intervention drug free days after initiation of the intervention, calculated on day 14.Need for ECMO.Ventilator free days on day 28.The use of drugs for PH treatment during the hospital admission.The use of pulmonary and/or cardiac medication at discharge and its total duration of administration.Short-term and long-term PH on echocardiography at 24 hours, 28 days/discharge and 6 and 12 months.The incidence of chronic lung disease.The development of neurological abnormalities evaluated with ultrasound of the brain before the start of the trial, after surgery and before discharge.The external validation of the sildenafil pharmacokinetic - pharmacodynamic (PKPD) model for the pharmacokinetics and the pharmacodynamic effects of sildenafil.

Safety outcomes include adverse events due to the study drugs and the vasoactive-inotropic support (VIS) score.

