Postnatally, infants are treated according to a standardised protocol for patients with CDH, which is implemented in all participating centres. This protocol was developed with the available evidence and consensus between the participating centres and was updated in June 2016.^10 16^ If the patient is diagnosed with PH in the first week of life, the patient will be allocated to one of the two study drugs (figure 1). iNO is provided by a tank connected to a ventilator. Different devices are used in different centres. Some centres use integrated systems, making it impossible to disconnect the iNO tank and replace it with another gas to facilitate a blinded intervention. Therefore, the study is open label. iNO is given with a starting dose of 20 ppm, which is the maximum dose.^18 19^ Sildenafil is given intravenously, using a loading dose of 0.4 mg/kg in 3 hours, followed by continuous infusion of 1.6 mg/kg/day.^20 21^ To wean the study drugs a standard protocol is followed (figure 2). The allocated drugs will be restarted as per protocol if criteria for its use are met again before the age of 14 days. To further standardise care, an inotropic support flow chart is included in the study protocol (figure 3). After day 14 treatment of PH will be at the discretion of the local medical team and the study drug can be changed to, for instance, sildenafil orally. The use of bosentan, milrinone and prostin next to the study treatment is allowed. The use of bosentan as add on therapy is allowed and is considered as PH treatment on day 14. The intervention will be prematurely stopped when the patient meets one or more of the defined failure criteria, described in point three of the secondary outcomes. Further treatment will then be at the discretion of the medical team and will be according to the standardised protocol.^16^ iNO and sildenafil can both be given outside the study protocol. An ECMO procedure may then be started in centres where ECMO is available. Data of all patients are used in the intention-to-treat analysis.

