### Sample size calculation

The sample size calculation is based on a power analysis for the primary outcome, using previously published data on PH. Lusk *et al* showed that PH, defined as >2/3 systemic blood pressure measured on echocardiography, in CDH patients on day 14 has a positive predictive value of 0.8 for death, death or ventilation, and death or ventilator support. PH on day 14 is observed in 64% of CDH patients.^24^

Even though the definition of the primary outcome is not the same, we assume a similar outcome percentage of 64% for failing the primary outcome in our trial, the absence of PH on day 14 without pulmonary vasodilator therapy and/or absence of death within the first 28 days of life, in the iNO group. Our aim is to promote practice change; therefore, we aim for a clinically significant difference. For a 25% relative reduction to 48%, a sample size of 300 patients (150 patients per group) is needed to obtain a power of 80%. This will match a number needed to treat of 6.25. Taking missing data and the effects of correction for covariates into account, we adjust this sample size to 330 patients. In the collaborating centres 550 patients will be born in 3 years. Based on our earlier trial (CMV Versus HFO in Congenital Diaphragmatic Hernia; VICI trial) we expect to have an inclusion rate of 60%. Therefore, the inclusion of 330 patients should be reached in 3 years.

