### Data analysis

The patients will be analysed according to the group they are randomised to (intention-to-treat analysis). A p-value (two-sided) <0.05 is considered significant in all analyses. The primary endpoint will be analysed using multiple logistic regression with randomisation arm, centre, observed/expected head-lung ratio, position of the liver, side of the defect, defect size and ventilation modality as independent variables.^25^ If necessary, multiple imputation using the fully conditional specification method will be used to account for missing data in the independent variables. We will perform a sensitivity analyses with adjustment for the use of prostin and milrinone, to account for the effects of these vasodilators on PH.

The following analyses will be performed for the secondary outcomes. The distribution of VIS score in all study participants will be compared between t=0 and t=12 hours after initiation of drug administration using a Wilcoxon signed rank test. The distribution of changes in OI and VIS score from t=0 to t=12 and t=24 hours will be compared between the randomisation groups with a Mann-Whitney test. The overall mortality in the first year of life will be compared between the randomisation groups with Kaplan-Meier curves and the log-rank test. The number of treatment failures, the need for ECMO (in ECMO centres) and the need for medication for PH or chronic lung disease at discharge, and during the first year of life, will be compared between randomisation groups with χ^2^ tests. The number of study drug free days at day 14, the number of ventilation-free days until day 28, the fraction of days with need for medical treatment (excluding the study drug) for PH during the hospital admission and the severity of chronic lung disease using the Bancalari definition will be compared between randomisation groups using Mann-Whitney tests. Deaths will be counted as the worst outcome in these analyses, in accordance with the intention-to-treat principle. The presence of PH at 28 days/discharge, 6 and 12 months according to the echocardiographic parameters will be compared between randomisation groups with a χ^2^ test.

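### The primary outcome is stated in two incompatible versions: treatment failure counts against an infant in the Objectives but not in the Abstract or the sample size section

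*Protocol article*

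**What the plan says.** Three places in the protocol article state the primary outcome with its components.

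- **Objectives**, where the outcome is formally defined: no PH on day-14 echocardiography, "without pulmonary vasodilator therapy and without treatment failure and/or death within the first 28 days after birth".
- **Abstract, Methods and analysis**: "Primary outcome is absence of PH on day 14 without pulmonary vasodilator therapy and/or absence of death within the first 28 days of life".
- **Sample size calculation**: "the absence of PH on day 14 without pulmonary vasodilator therapy and/or absence of death within the first 28 days of life". The 64% assumed for failing the outcome in the iNO group is attached to this wording.

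The strengths and limitations box refers to the primary outcome simply as PH. That is shorthand and is not treated here as a further definition.

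Treatment failure is a separate event with its own criteria (saturation, CO2, lactate and pH, hypotension, oxygenation index). It is also listed as a secondary outcome: "The incidence of treatment failure which is defined as". Under Randomisation, intervention and blinding, meeting a criterion ends the study intervention. Both drugs may then be given outside the protocol, ECMO may be started where available, and the infant stays in the intention-to-treat analysis.

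On add-on drugs, the same section allows bosentan, milrinone and prostin and says: "The use of bosentan as add on therapy is allowed and is considered as PH treatment on day 14". Data analysis plans a sensitivity analysis with "adjustment for the use of prostin and milrinone, to account for the effects of these vasodilators on PH".

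**The concern.** Data analysis fits one logistic regression to one binary primary endpoint and does not say which version it uses. The choice matters because the trial is open label and permits the other arm's drug after failure. If treatment failure is a component, an infant who needed rescue is a failure whatever happens later, and the endpoint is close to a comparison of the two drugs as first treatment. If it is not, an infant rescued by the other drug or by ECMO can still be a success for the arm to which it was randomised, and the endpoint compares two strategies with rescue. Both are legitimate questions, but one trial result cannot answer both. The published protocol is also what readers will use to check the reported outcome, and at present it supports two answers.

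**Working it through.** **1. The plan's own figure.** Inputs from Sample size calculation and Data analysis: p1 = 0.64, p2 = 0.75 × 0.64 = 0.48, two-sided 5%, power 80%, equal groups. Mean proportion p̄ = 0.56.

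n per group = [1.960·√(2p̄(1−p̄)) + 0.842·√(p1(1−p1) + p2(1−p2))]² / (p1−p2)²

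= [1.960 × 0.7020 + 0.842 × 0.6928]² / 0.16² = 1.959² / 0.0256 ≈ 150.

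This reproduces the stated 150 per group (300 in total). The arithmetic is sound; the conflict is in the definition.

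**2. The two definitions side by side.** Let D14 mean no PH and no pulmonary vasodilator therapy on day 14. In the Objectives, and/or joins two unfavourable events after the word without, so the natural reading is that neither may occur. In the Abstract and Sample size calculation, and/or is read here as 'and' (see the objection below).

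| D14 met | Treatment failure | Dead by day 28 | Objectives | Abstract and Sample size |
|---|---|---|---|---|
| yes | no | no | success | success |
| yes | no | yes | failure | failure |
| **yes** | **yes** | **no** | **failure** | **success** |
| yes | yes | yes | failure | failure |
| no | no | no | failure | failure |
| no | no | yes | failure | failure |
| no | yes | no | failure | failure |
| no | yes | yes | failure | failure |

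The versions disagree in one state of eight: the infant who met a failure criterion and recovered. The rescue provisions make that state possible, so it is not an empty cell by design.

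**3. Effect on the planning rate.** The 64% is a published rate of PH on day 14. The article says that its own definition differs from that source, but not that the sample size wording differs from the Objectives. The control failure rate under either version is not given. Adding a component can only raise the failure rate or leave it unchanged. If a share x of control infants falls in the discordant state, 64% under the sample size wording becomes 64% + x under the Objectives. Values of x are assumptions; the 25% relative reduction is kept.

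Power at 150 per group = Φ{[(p1−p2)·√150 − 1.960·√(2p̄(1−p̄))] / √(p1(1−p1) + p2(1−p2))}

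| Assumed x | Control rate | Sildenafil rate | Power |
|---|---|---|---|
| 0 | 64% | 48% | 80% |
| 6 points | 70% | 52.5% | 88% |
| 10 points | 74% | 55.5% | 92% |
| 16 points | 80% | 60% | 97% |

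On these assumptions, including treatment failure does not cost power. That holds only if the relative reduction carries over to the wider endpoint, which the document does not address.

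**The case against.** The strongest reply is that the Objectives section is where the outcome is formally defined, that the other two places only restate it, and that the full protocol or an analysis plan may settle the matter. Part of this stands: the Objectives version is the natural one to keep, and nothing suggests that a version would be chosen after seeing data. But Sample size calculation is body text, so abbreviation of an abstract does not explain the omission there. The article contradicts itself rather than leaving something out, and an unseen document cannot make its sections agree.

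It is also fair to say that no sizing failure follows. The 150 per group reproduces, and the discordant group has unknown size.

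Two stronger readings are tempting and are not supported:

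- A reader might take and/or before absence of death literally as 'or', so that every infant alive at day 28 is a success, and conclude that there is a third definition and a trial powered for the wrong event. The context rules this out. The sample size section uses a day-14 PH rate as the rate of failing the outcome, which makes no sense if survivors with PH succeed, and the Objectives make PH and death each disqualifying. Nor could the 27% mortality in the Introduction size such an endpoint: it is for CDH overall, with no time window. What remains is loose wording.
- A reader might infer that bosentan is the sole add-on drug that counts on day 14. The text says that bosentan counts; it does not say that others do not. The sensitivity analysis for prostin and milrinone is compatible with their not counting. This is an ambiguity, not a contradiction.

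**Conclusion.** The point holds as an internal inconsistency in the primary outcome. Treatment failure is a component in the Objectives and is absent from the Abstract and from the sample size section that carries the 64%. An infant who met a failure criterion, is PH-free and off vasodilators on day 14 and is alive at day 28 is classified in opposite ways. This conclusion does not depend on how and/or is read.

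The consequence is interpretive: it is not settled which question the single binary analysis answers. The number of infants affected cannot be determined from the document, and no loss of power is shown. It should be corrected because it concerns the primary endpoint and neither abbreviation nor a separate analysis plan reconciles the sections.

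**What to change.** Use one definition in the Abstract, Objectives and Sample size calculation, written as a conjunction. Success means all of:

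- alive at day 28;
- no echocardiographic PH on day 14;
- no pulmonary vasodilator therapy on day 14;
- no treatment failure, as in the Objectives, with its time window stated. The present sentence leaves open whether the 28 days apply to treatment failure or only to death.

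Failure is any component not met. State that the 64% is the assumed failure rate for this definition, and name it as the endpoint of the logistic regression. (The Abstract's own starting rate of 68% is a separate discrepancy.)

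Two wording changes go with it: replace and/or before absence of death with 'and', and state whether milrinone and prostin, which Data analysis calls vasodilators, count as pulmonary vasodilator therapy on day 14 for the endpoint.

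The cost is text only. Day-14 echocardiography is in Table 1, and mortality, treatment failure and use of PH drugs are already planned outcomes, so no new data collection is needed. The sample size need not change if the sponsor stands by 64% for the unified definition.

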### Patients

Infants diagnosed with CDH who have PH in the first week after birth are eligible for the trial if born at or after a gestational age of 34 weeks. The diagnosis of PH is defined as at least two of the following four criteria: (1) systolic pulmonary arterial pressure >2/3 systolic systemic pressure estimated by echocardiography, (2) RV dilatation/septal displacement, RV dysfunction +/−left ventricular dysfunction, (3) pre-post ductal SpO_2_ difference >10%, (4) OI >20. Exclusion criteria are a severe chromosomal anomaly which may imply a decision to stop or not to start life-saving medical treatment, severe cardiac anomaly expected to need corrective surgery in the first 60 days of life, renal anomalies associated with oligohydramnios, severe orthopaedic and skeletal deformities, which are likely to influence thoracic, and/or lung development and severe anomalies of the central nervous system. Patients who are born in another centre and transported with iNO are also excluded from the trial. Patients who received fetal interventions (trachea balloon placement) are not excluded.

Following antenatal diagnosis, the parents are counselled and informed about the study by the clinician or research coordinator. Also, they receive a patient information letter and an informed consent form. If the patient is not born in a participating centre or the diagnosis of CDH was not known, parents are counselled after the diagnosis of CDH and are informed about the study. Also, they receive written information and an informed consent form. This informed consent form contains consent for the trial and for collection of data and material for future research.

For the development of the protocol the SPIRIT reporting guidelines have been used.^17^ This publication is based on protocol V.4, 13 June 2018.

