#### ​Follow up

After day 14, additional clinical data, such as time on ventilator support (days) and the use of drugs for the treatment of PH, are collected to answer the secondary outcome questions. Also, echocardiographic measurements are taken at 6 and 12 months to evaluate the presence of chronic PH (table 1).

**Table 1 T1:** Procedures and measurements

	Day 0–7 before start therapy	3 hours after start sildenafil	12 hours after start	8 am after start	24 hours after start	Day of surgery, preoperatively	Day after surgery	Day of ECMO, pre- cannulation	8 am after start ECMO	Day 14	Day 28/before discharge	Day 56	6 months	12 months
Echocardiography	X				X					X	X		X	X
Calculation OI	X		X		X									
Calculation VIS score	X		X		X									
Blood sample	X			X		X	X	X	X	X				
Tracheal aspirate	X			X		X	X	X	X	X				
Urine sample	X			X		X	X	X	X	X				
Severity of CLD											X	X		
Ultrasound brain	X						X							
Sildenafil plasma level		X		X		X	X		X					

CLD, chronic lung disease; ECMO, extracorporeal membrane oxygenation; OI, oxygenation index; VIS, vasoactive-inotropic support.

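### Drug-free days are counted from drug start to day 14, so the counting window shrinks from 14 to 7 days with age at start, and the plain Mann-Whitney test mixes that age with time on drug (minor)

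*Protocol article*

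**What the plan says.** Under Objectives, the secondary outcome time on intervention drug is defined as "intervention drug free days after initiation of the intervention, calculated on day 14". The Data analysis section names the analysed quantity as "The number of study drug free days at day 14" and compares it between arms with a Mann-Whitney test. Deaths count as the worst outcome, and no adjustment is stated.

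Three places set when the drug can start:
- Patients: "Infants diagnosed with CDH who have PH in the first week after birth are eligible for the trial".
- Randomisation, intervention and blinding: "If the patient is diagnosed with PH in the first week of life, the patient will be allocated to one of the two study drugs".
- Table 1 (Follow up), heading of the baseline column: "Day 0–7 before start therapy".

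Two sentences under Randomisation, intervention and blinding bear on what day 14 means: "The allocated drugs will be restarted as per protocol if criteria for its use are met again before the age of 14 days", and "After day 14 treatment of PH will be at the discretion of the local medical team". In Table 1, Day 14 is a column of its own, apart from the columns counted in hours after start.

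**The concern.** Counting begins at an event whose date differs between infants and ends at what appears to be a fixed age. The maximum score therefore differs between infants for a reason unrelated to how long they need the drug. An infant who starts late cannot reach the score of one who starts early, however short the treatment.

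The outcome is labelled as time on drug, but the score equals the available window minus time on drug. Age at start enters it one day for one day. A test that ranks all infants together treats this component as part of the response. The stakes are the precision of the comparison, its sensitivity to a chance imbalance in start age, and the meaning of the reported median. The primary outcome is not involved.

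**Working it through.** **The plan's own figures.** The article gives no figure for this outcome. Its only power calculation is for the primary outcome, and it reproduces. For 64% against 48%, two-sided 0.05 and 80% power, n per arm = [1.960·√(2·0.56·0.44) + 0.842·√(0.64·0.36 + 0.48·0.52)]² / 0.16² = 150, or 300 in total, raised in the article to 330. Nothing below changes that. It supplies only the arm size used here, 330/2 = 165.

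**Window.** Inputs are start on day 0 to 7 (Table 1) and an end at age 14 days (restart rule in Randomisation, intervention and blinding). Window = 14 − age at start.

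| Start day | 0 | 1 | 2 | 3 | 4 | 5 | 6 | 7 |
|---|---|---|---|---|---|---|---|---|
| Window (days) | 14 | 13 | 12 | 11 | 10 | 9 | 8 | 7 |

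**Score.** Score = (14 − age at start) − days on drug.
- Same exposure, different score: 4 days on drug give 14 − 4 = 10 for a day-0 start and 7 − 4 = 3 for a day-7 start.
- Reversed order: 3 days on drug from day 7 give 7 − 3 = 4, while 9 days on drug from day 0 give 14 − 9 = 5. The infant with a third of the exposure ranks worse.

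**Illustrative size.** The article gives neither the start-age distribution nor the distribution of time on drug, so these are assumptions: 165 per arm; gamma durations of shape 2 and mean 6 days, 25% shorter in one arm; 20% deaths ranked worst; two-sided 0.05. The plain Mann-Whitney test is compared with a van Elteren test stratified by day of entry, with the drug assumed to start on the day of randomisation. Reversed pairs are the share of surviving pairs with different durations in which the infant with less time on drug gets the lower score.

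| Start ages | Power, plain | Power, stratified | Difference (points) | Reversed pairs |
|---|---|---|---|---|
| Uniform over day 0-7 | 43% | 57% | 14 | 14% |
| 60% on day 0-1 | 44% | 56% | 12 | 13% |
| 80% on day 0-1 | 47% | 56% | 9 | 8% |
| 95% on day 0-1 | 53% | 56% | 3 | 2% |

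**Dependence on the shape.** Plain against stratified power:
- Shape 1: 25% vs 30% with uniform starts; 28% vs 29% with 95% on day 0-1.
- Shape 4: 63% vs 84% with uniform starts; 83% vs 85% with 95% on day 0-1.

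Across these assumptions the gap runs from about 1 to about 21 points.

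**Type I error.** In a second simulation with log-normal durations, the rejection rate of the plain test under no difference lay between 0.04 and 0.06 for every start-age pattern tried. There is no sign of inflation.

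**The case against.** **Randomisation balances start age.** This stands. PH is diagnosed before allocation, so age at entry is balanced in expectation. A reader might infer from the unequal windows that the comparison is biased or the p-value invalid. The documents do not support that, and the type I error check agrees.

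**Day 14 could mean 14 days after initiation.** On that reading every infant has the same 14-day window and the mechanism disappears. The restart rule and the layout of Table 1 point to postnatal age instead, but the outcome definition itself does not say so. The alternative would also carry a day-7 starter to age 7 + 14 = 21 days, a week beyond the age at which treatment passes to the local team. It is tempting to add that a later switch to oral sildenafil would then score as drug-free. The article says nowhere how such days are scored, so that step is not supported.

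**Most infants probably start early.** This is plausible. The Introduction ties PH in CDH to a failure of the fall in resistance immediately after birth, and the article describes antenatal diagnosis and planned delivery. The article gives no distribution, however, and allows a full week. The uniform case is therefore an upper illustration, not an estimate.

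**The trial is powered only for the primary outcome.** This is correct, so no promised power is lost, and it keeps the severity low.

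**This could be left to the analysis plan.** The point does not rest on a missing detail. The article states the start of the count, its end and the test, and the combination is inefficient. Precision can be gained almost for free from an age known at entry.

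**Conclusion.** The point holds as a minor one. If day 14 is a postnatal age, as the surrounding text suggests, the counting window varies from 14 to 7 days, and the plain Mann-Whitney test ranks infants on a mixture of age at start and time on drug. The between-arm comparison remains unbiased with valid type I error. The cost is lost precision on one secondary outcome and a median that cannot be read directly as time on drug.

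The size cannot be fixed from the article. Under shape-2 gamma durations it runs from 3 power points with 95% of starts on day 0-1 to about 14 with uniform starts, and other shapes widen that range. These figures show how the mechanism scales. They do not measure a loss in this trial, and the largest of them should not be quoted as its effect.

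**What to change.** 1. In the outcome definition, state that day 14 is age 14 days for this outcome, and use the same wording in the Data analysis section.
2. Replace the plain Mann-Whitney test for this outcome with a van Elteren test stratified by age in days at randomisation (for example 0, 1, 2-3 and 4-7), or with a proportional-odds model that has that age as a covariate. Use age at randomisation and not age at drug start: the latter arises after randomisation in an open-label trial and is undefined for an infant who never starts.
3. Include all randomised infants and keep deaths as the worst rank.
4. Report the median drug-free days by arm together with the available window. Stratification repairs the comparison but not the median, which still depends on the window.

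The cost is one sentence in the definition and a slightly more complex test for one secondary outcome. Age at entry has to be known to confirm eligibility in the first week, so no additional patients or procedures are needed. The change should be made before outcome data are examined by arm.
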